### Trial design

This is an adaptive, two-stage randomised phase IIa, single-centre clinical trial that will aim to recruit 30 patients with severe Graves’ disease from secondary care at the Newcastle upon Tyne Hospitals NHS Foundation Trust. It is a single-blinded trial in which participants will be blind to allocation. Recruitment start date: October 2021; planned end of trial (last patient last visit): April 2024.

Stage 1 is a dose–response study using four doses of daratumumab (9 mg/kg, 3 mg/kg, 1 mg/kg, 0.5 mg/kg) and a colourless, volume-matched placebo infusion in approximately 15 patients (ie, five groups of n=3, randomised in a 1:1:1:1:1 ratio using permuted random blocks without stratification) (figure 1).

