**Figure 1 F1:**
[figure not shown]
Design of the study. TRAb, thyroid-stimulating hormone receptor antibodies.

Following stage 1, an interim analysis will be performed of the first 15 patients in order to select an optimal dose(s) of daratumumab for stage 2. The dose selection will be based on an analysis of the reduction in TRAb concentration and safety assessed at 12 weeks. In stage 2, the remaining 15 patients will be randomised between placebo and one or two chosen doses of daratumumab depending on results of the interim analysis. Patients in both stages of the study will have all the same assessments and will be followed up for 24 weeks, with the primary endpoint being measured at week 12.

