### Randomisation

Randomisation will be performed by delegated and trained members of the site research team using the online system ‘Sealed Envelope’—a central, secure, 24-hour web-based randomisation system. In both stages, the allocation sequence will be computer generated using a random permuted block design. Patients will be randomly allocated equally to the available daratumumab doses or to a matched placebo; for example, if two doses of daratumumab plus placebo are to be used, the allocation would be 1:1:1. There are no stratification factors.

In stage 1, patients will be allocated to receive a dose of daratumumab (9, 3, 1, 0.5 mg/kg) or matched placebo. In stage 2, patients will be allocated to receive daratumumab (one or two dose levels as determined by the interim analysis) or matched placebo.

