### Intervention

Each participant will receive two infusions, on day 0 and day 14 (±3 days). The prescribed daratumumab dose will be prepared in a 500 or 1000 mL bag of sodium chloride 0.9%, using the most recent available participant weight to calculate banded dose (see table 2 for volume and infusion rate). Each participant will be prescribed the same banded dose for both infusions, using the same weight for both. Where placebo is allocated, a volume-matched bag of sodium chloride 0.9% will be used. All participants will be pre-medicated with three non-IMPs, paracetamol (1 g orally), methylprednisolone (100 mg intravenously) and chlorphenamine (10 mg intravenously) at least 30 min prior to their allocated infusion.

**Table 2 T2:** Infusion rate table

Time (hour:min)	Rate (mL/hour)	Total volume at end of time (mL)
Stage 1 (1000 mL)		
1	80	80
2	160	240
3	240	480
4	320	800
4:40	320	1000
Stage 2 rate A (1000 mL)		
1	50	50
2	100	150
3	150	300
4	200	500
5	200	700
6	200	900
6:30	200	1000
Stage 2 rate B (500 mL)		
1	50	50
2	100	150
3	150	300
4	200	500

The maximum infusion rate of daratumumab was determined by the recommendation of the SmPC for daratumumab (DARZALEX 20 mg/mL concentrate for solution for infusion). For stage 1, all participants will receive the IMP/placebo diluted in 1000 mL sodium chloride 0.9% for both infusions. For stage 2, some patients may receive higher doses of daratumumab, so a more prolonged first infusion will be given to all participants. If participants have no IRRs during their first dose in stage 2, then the second dose may be given in 500 mL sodium chloride 0.9% with a faster infusion rate, in line with SmPC recommendations.

IMP, investigational medicinal product; IRRs, infusion-related reactions; SmPC, Summary of Product Characteristics.

Vital signs (pulse rate, blood pressure and temperature) will be recorded prior to the start of each infusion and every 15 min during the course of the infusion, and for 1 hour afterwards. Infusion-related reactions will be addressed as shown in table 3, and documented as an AE. Infusion charts will be completed to document compliance with prescribed dose. Participants will be followed up by phone approximately 2 days after each infusion visit to check for any AEs. After the day 14 visit, no further IMP will be administered. Patients will continue their regular medications, including antithyroid drugs and beta-blockers throughout the study, as deemed appropriate by the clinical team.

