### Analysis

The primary analysis will assess whether there is a significant dose–response using percentage reduction in serum TRAb concentration from baseline to 12 weeks using the intention-to-treat population (participants analysed according to randomisation allocation).

To do this, we will calculate a contrast-based test statistic at a one-sided 5% type I error rate.^21^ If this test statistic is significant, we will test whether there is a mean difference in the outcome between individual doses and placebo using a suitable linear model. We will also perform a simple test of all placebo participants versus all daratumumab patients using a linear model that adjusts for presence of eye disease. We will also fit quadratic and three-parameter Emax models to assess dose–response.^22^ This analysis will inform selection of the most suitable dose for subsequent trials. Exploratory analyses using subgroups of patients including by gender, smoking status, presence of TED and change in serum TRAb will be undertaken.

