### Interim analyses and criteria for the premature termination of the trial

An interim analysis of dose–response will be conducted after 15 patients have provided 12-week follow-up data. To assess efficacy, a three-parameter Emax model will be fitted to the logarithm of the percentage change in TRAb from baseline to week 12 using the DoseFinding package in R^23 24^ in the dose–response population (participants analysed according to the amount of daratumumab received). This model is used to estimate the plateau effect and (1) the dose that gives a mean reduction of 50% and (2) the dose that gives 90% of the plateau effect. If the estimated plateau effect corresponds to >50% reduction in TRAb, the trial will continue with placebo and doses (1) and (2) defined above. If the estimated plateau corresponds to less than 25% reduction in TRAb, the trial will terminate early for lack of promising dose–response unless the Data Monitoring Committee (DMC) agrees that there has been an unequivocal improvement in serum thyroid hormone measurements in the active IMP versus placebo groups; if it is between 25% and 50% reduction, the trial will continue with doses of 9 mg/kg and a higher daratumumab dose (eg, 12 or 16 mg/kg as determined by safety data), plus placebo. Safety information will be taken into consideration in deciding stage 2 dose(s) and could over-ride the model-based dose recommendations.

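### The all-placebo versus all-daratumumab model adjusts for eye disease but not for stage, although the placebo share changes from 1/5 to 1/3 or 1/2 between stages

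*Protocol article*

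**What the plan says.** **Allocation.** Trial design describes stage 1 as "five groups of n=3, randomised in a 1:1:1:1:1 ratio using permuted random blocks without stratification". For stage 2, "the remaining 15 patients will be randomised between placebo and one or two chosen doses of daratumumab". The Randomisation section adds "Patients will be randomly allocated equally to the available daratumumab doses or to a matched placebo", and, as an example, "if two doses of daratumumab plus placebo are to be used, the allocation would be 1:1:1". Placebo is therefore 3/15 = 1/5 of stage 1 and 1/3 or 1/2 of stage 2.

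**Doses.** Under the interim rules, if the estimated plateau exceeds a 50% reduction, "the trial will continue with placebo and doses (1) and (2) defined above". Those doses come from the fitted curve and need not match any stage 1 dose. In the 25-50% band, stage 2 uses 9 mg/kg and a higher dose that stage 1 did not use.

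**Analysis.** First, "we will calculate a contrast-based test statistic at a one-sided 5% type I error rate". If it is significant, individual doses are compared with placebo in a linear model whose covariates are not named. The plan also includes "a simple test of all placebo participants versus all daratumumab patients using a linear model that adjusts for presence of eye disease". The Analysis section does not mention stage.

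**Conduct.** The infusion schedule differs by stage. In stage 2 some patients may receive higher doses, "so a more prolonged first infusion will be given to all participants".

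**The concern.** Randomisation makes placebo and active patients comparable within a stage. Across stages the chance of receiving placebo differs, so a crude pooled comparison mixes the treatment effect with any difference between the stages. Adjusting for eye disease is reasonable in itself, but it does not deal with this. Eye disease plays no part in the allocation, whereas stage sets the allocation ratio.

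Some drift is plausible:
- Recruitment starts in October 2021 and the last visit is planned for April 2024.
- Stage 2 doses depend on 12-week data from 15 patients.
- Background antithyroid treatment is left to the clinical team.
- The first infusion is longer in stage 2.

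None of these gives a size for the drift. At stake is the comparison that asks most simply whether daratumumab lowers TRAb at all.

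**Working it through.** **1. The plan's own power.** A two-stage simulation (3,000 replicates) used log(week 12/baseline TRAb) with SD 0.5, a 5% placebo reduction, 3 per arm in stage 1, the stated interim rules, 12 patients at 1:1:1 in stage 2 (N = 27) and a one-sided 5% Emax contrast with guessed ED50 of 1 mg/kg and no stage term.

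| Table 5 scenario | Stated | Simulated |
|---|---|---|
| 1 | >99% | 99.7% |
| 2 | 92% | 93.7% |
| 3 | 83% | 85.2% |
| Null | 3.2% | 2.7% |

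The agreement is close enough to use this model. The R supplement was not available, so the response scale, the guessed ED50, 16 mg/kg as the higher dose and a 0.1-16 mg/kg limit on fitted doses are assumptions.

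**2. Bias in the pooled comparison.** Let δ be the mean TRAb change in stage 2 minus that in stage 1 at the same treatment; positive δ means a smaller fall in stage 2. Without a stage term,

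bias (active minus placebo) = δ × (share of active patients from stage 2 − share of placebo patients from stage 2).

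- Two stage 2 doses, 5 per arm: 10/22 − 5/8 = 0.455 − 0.625 = −0.170.
- One dose, 7 placebo and 8 active: 8/20 − 7/10 = −0.300.
- One dose, 8 placebo and 7 active: 7/19 − 8/11 = −0.359.

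Positive δ therefore favours the drug in this test.

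**3. Effect on one-sided error.** The protocol states the 5% level for the contrast test; the same level is assumed here. SD is 25 and N is 30. Unadjusted SE = 25 × √(1/n placebo + 1/n active): 10.3 with two doses, 9.68 or 9.47 with one. Unmodelled drift also inflates the residual SD to about √(625 + δ²/4): 25.5 for 10 points and 26.9 for 20. The effective critical value becomes 1.645 × 25.5/25 = 1.68 or 1.645 × 26.9/25 = 1.77. Subtracting bias/SE gives the normal tail.

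| Assumed δ | Two doses | One dose |
|---|---|---|
| 10 | 1.68 − 0.165 = 1.51: 6.5% | 1.68 − 0.31 to 0.38: 8.6-9.7% |
| 20 | 1.77 − 0.33 = 1.44: 7.5% | 1.77 − 0.62 to 0.76: 12.5-15.5% |

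Simulation agrees: about 7-8% with two doses and 9-15% with one. With a stage term it is about 5%. Drift in the other direction costs power instead. In scenario 2 with N = 30 and a log drift of −0.4, the pooled test has 74.2% power without stage and 89.8% with it.

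**4. The other analyses, only if they too omit stage.**
- *Emax contrast, two stage 2 doses:* null rejection of about 6-8% for 10-20 points of drift in the drug's favour. Here the favourable direction is negative δ, the opposite of the pooled test, so drift alone could make the two analyses disagree.
- *Dose given in stage 1 only, against all placebo:* 0 − 5/8 = −0.625δ, or 12.5 points for an assumed 20.
- *Dose given in stage 2 only:* 1 − 5/8 = +0.375δ, or 7.5 points for an assumed 20.
- *Dose carried through in equal numbers with placebo:* 5/8 − 5/8 = 0.

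**5. Cost of the stage term.** The adjusted variance factor is 1/(sum over stages of n placebo × n active / n stage).
- Two doses: 1/(36/15 + 50/15) = 0.1744, against 0.1705; √(0.1744/0.1705) gives SE +1.2%.
- One dose: 1/(36/15 + 56/15) = 0.1630, against 0.150 or 0.1435; SE +4.3% or +6.6%.
- Contrast power, N = 27: 93.7% to 91.4% in scenario 2 and 85.2% to 83.2% in scenario 3.

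**The case against.** **Most of the analysis is not specified as omitting stage.** A reader might infer that the primary contrast and every dose-versus-placebo estimate are pooled without stage. The article does not say so. It names no covariates for the contrast test and only a suitable linear model for individual doses, and the analysis plan may settle both. This objection stands. The fault is stated only for the pooled test.

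**Drift does not bias every contrast, and nothing is fully confounded.** A carried-over dose is unbiased. Placebo is present in both stages, so doses used in different stages can still be compared once stage is in the model, with wider intervals. This also stands.

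**Large error rates for single doses ignore the gate.** Taken alone, an unadjusted test of a stage-1-only dose under a 20-point drift would reject about 16% of the time. But individual doses are tested only after a significant contrast. The drift direction that favours a stage-1-only dose (positive δ) lowers the unadjusted contrast's null rejection to 3.2% or 1.6% (log drifts of 0.2 and 0.4, two stage 2 doses), and the gated error cannot exceed that under the global null. The 16% should not be quoted as a trial error rate.

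**The drift is assumed and may be small.** The outcome is within-patient change at one centre, the protocol assumes only a 5% placebo reduction, and no route from infusion rate to week 12 TRAb is offered. With two doses, a 0.2 log drift biases the pooled estimate by 0.034 against an SE of 0.206. On mean squared error, the unadjusted pooled estimate is better when drift is below about 9 points (25 × √(0.1744 − 0.1705)/0.170). This limits the severity, but it does not justify omitting stage from a test: below that point the loss from adjusting is small, while above it the unadjusted test loses its nominal level.

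**Conclusion.** The point holds for the pooled placebo-versus-daratumumab model as written. The allocation ratio changes by stage, the only adjustment named is eye disease, and between-stage drift does not cancel.

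The effect is modest with two stage 2 doses and larger with one. The interim rules name two doses whenever the trial continues on the fitted plateau alone, but the protocol allows one and lets safety findings override the rules.

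For the contrast test and the individual doses the conclusion is conditional on their also being fitted without stage, which the article leaves open. It would be wrong to say that adjustment is free: contrast power falls by about 2 points, staying above the 90% target in scenario 2. The bias shares are exact for the planned numbers. The error rates rest on the assumed 10-20 point drift, SD 25, N = 30 and no early stop.

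**What to change.** Add stage (1 or 2) as a fixed factor, beside eye disease, to the all-placebo versus all-daratumumab model. State the same for the contrast test and the dose-versus-placebo models, and give the Emax and quadratic fits a stage-specific intercept.

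Stage 2 was under way when the article was written, so this should be fixed in the analysis plan before the final analysis. It changes nothing in the conduct of the trial and needs no new data. Beyond the one degree of freedom and the losses in SE and power shown in the working, the price is wider intervals for doses given in one stage only, which reflect how little within-stage placebo information those doses have.

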### Interim analyses and criteria for the premature termination of the trial

An interim analysis of dose–response will be conducted after 15 patients have provided 12-week follow-up data. To assess efficacy, a three-parameter Emax model will be fitted to the logarithm of the percentage change in TRAb from baseline to week 12 using the DoseFinding package in R^23 24^ in the dose–response population (participants analysed according to the amount of daratumumab received). This model is used to estimate the plateau effect and (1) the dose that gives a mean reduction of 50% and (2) the dose that gives 90% of the plateau effect. If the estimated plateau effect corresponds to >50% reduction in TRAb, the trial will continue with placebo and doses (1) and (2) defined above. If the estimated plateau corresponds to less than 25% reduction in TRAb, the trial will terminate early for lack of promising dose–response unless the Data Monitoring Committee (DMC) agrees that there has been an unequivocal improvement in serum thyroid hormone measurements in the active IMP versus placebo groups; if it is between 25% and 50% reduction, the trial will continue with doses of 9 mg/kg and a higher daratumumab dose (eg, 12 or 16 mg/kg as determined by safety data), plus placebo. Safety information will be taken into consideration in deciding stage 2 dose(s) and could over-ride the model-based dose recommendations.

### Statistical size calculations

A 50% or more reduction in TRAb concentration from baseline within 12 weeks of intervention was chosen as biologically plausible and clinically important. An observational study of patients with milder Graves’ disease showed a mean change in TRAb concentration of 2% over 6 weeks, with a standard deviation (SD) of 15%. Assuming an SD of 25%, to account for the outcome being measured at 12 weeks, a 5% reduction in placebo-treated subjects, an Emax dose–response, a plateau 60% reduction in TRAb concentration over 12 weeks with active IMP and 1 mg/kg dose giving half of the total, 27 participants will give over 90% power (5% one-sided type I error) to conclude there is a dose–response relationship. In order to allow for 10% dropout, we will plan to recruit 30 participants.

Power was verified through simulations in ‘R’,^24^ assuming the logarithm of the percentage reduction to be normally distributed with SD of 0.5 (equivalent to 25% SD when the mean is 50% reduction). The power/type I error rate for a range of scenarios is given in table 5.

**Table 5 T5:** Power/type 1 error rate calculations

Scenario	Probability to conclude dose–response (10 000 replicates)
1—plateau of 80% reduction ED50=3 mg/kg	>99%
2—plateau of 60% reduction, ED50=1 mg/kg	92%
3—plateau of 60% reduction, ED50=3 mg/kg	83%
4—null scenario	3.2%

The R code required to reproduce these results can be found in online supplemental material 1.

ED50, median effective dose.

10.1136/bmjopen-2023-079158.supp1Supplementary data

### Trial oversight

The TMG will meet approximately monthly throughout the trial, and includes the Chief Investigator, statisticians, NCTU staff, pharmacy and sponsor representatives. Oversight is provided by an independent DMC that will meet at the start of the trial, at the interim analysis point and on an ad hoc basis throughout, as well as a Trial Steering Committee (TSC) that will generally meet following a DMC meeting. The terms of reference and composition of these committees are outlined in their respective charters.

### Protocol amendments

NCTU will submit amendments to the Health Research Authority and MHRA/REC (as appropriate) as well as informing ISRCTN, trial recruiters, investigators and the relevant research and development department of changes. A list of version changes will be kept in the trial protocol appendix and can be found in online supplemental material 2.

10.1136/bmjopen-2023-079158.supp2Supplementary data

### Trial status

This manuscript is based on protocol V.6.0 dated 18 May 2023. The Graves-PCD trial opened to recruitment on 29 September 2021. At the time of writing, stage 2 of the trial is underway.

### Patient and public involvement

Patients were involved in the design of the trial via the BTF (https://www.btf-thyroid.org/), and lay members will have oversight and input during the trial and dissemination as members of the TSC.

## Ethics and dissemination

The trial received a favourable ethical opinion from London-Hampstead REC (reference 21/LO/0449). The results of this trial will be disseminated at international meetings, in the peer-reviewed literature and through partner patient group newsletters and presentations at patient education events.
